## 10.2 Study Termination

Termination of the study before all subjects have been enrolled can occur for any of the following reasons:

- the Swedish Authorities requested termination of the study;
- it was determined that the risk level associated with the experimental drug was significant and warranted termination of the study;
- the sponsor terminated the study for any reason, at any time, by written notice of intended termination;
- the principal investigator, REG or MPA terminated participation of that clinical site in the study by written notice;
- any other clause in the individual site Clinical Study Agreement was not met

## 10.3 Data Recording

Source documents are original documents, data, and records from which the subject's case report form (CRF) data are obtained. These may include but are not limited to hospital records, clinical and office charts, laboratory and pharmacy records, diaries, microfiches, radiographs, and correspondence. All original source documents supporting entries on CRFs must be maintained and be readily available.

The investigator will record all data with respect to the study in the subject's CRFs. This includes but is not limited to study procedures, laboratory data, safety-related data and drug accountability.

The investigator will sign and date the indicated places on the CRFs. These signatures will signify that the investigator inspected or reviewed the data on the CRF and on the data queries and that he/she agrees with the content.

All corrections on a CRF and on source documents must be made in a way that does not obscure the original entry. The correct data must be inserted, dated and initialed by study center personnel. If the reason for the change is not obvious, an explanation should be provided.

#### **10.4 Case Report Forms**

The Investigator will complete Case Report Forms for all subjects. These are to be completed in English. If a test/assessment is not done and will not be available, indicate this by writing "N/D" (Not Done) in the respective answer field in the CRF. If the question is irrelevant (e.g. is not applicable) indicate this by writing "N/A" (Not Applicable) in the respective answer field.

Corrections of data can only be made by crossing out the incorrect data and writing the correct data next to those crossed out (e.g. ~~352~~ 325). Erasure by any method is not allowed. Any changes in the CRF by the Investigator or his/her delegate must be signed with initials, dated and explained (if necessary). If corrections are made by the Investigator's authorised staff after the date of the Investigator's signature on the CRF, the CRF must be signed and dated again by the Investigator. Corrections necessary after the CRFs have been removed from the Investigator's site must be documented on a Data Clarification Form (DCF).

Original source documents, case report forms, and other study documentation will be maintained at the study site as specified.

Completed original Case Report Forms are the property of the Sponsor.

#### **10.5 Training**

The Investigator will ensure that appropriate training relevant to the study is given to the medical, nursing and other staff involved. Any information of relevance to the performance of this study is to be forwarded to the co-Investigator and other staff involved.

All investigators signing the protocol and key personnel should provide signed and dated Curriculum Vitae (CV) originals to be filed by the Sponsor. The CV should include name, title, occupation, education, research experience and present and former positions. A staff signature list including delegation responsibilities is required and will be continuously up-dated.

#### **10.6 Source Data**

Source data will be collected in the "Source Data File". The Source Data File should contain raw data from examinations/samplings/laboratory results required to verify the data entered into each patient's CRF.

The following data will be recorded directly on the CRFs and will be considered source data: Gender, age, length, weight, HC, medical history, physical examination and retinal scan.

The hospital records should clearly indicate at least:

- that the patient participated in the study (by patient identification and study identification)
- when the written informed consent was obtained,
- all examinations/samplings/laboratory results of importance for the patient's clinical care and
- serious adverse events.

### **10.7 Quality Assurance**

The data will be entered into a database, where internal review and programmed computer checks will be used to identify selected protocol violations and data errors. If necessary, requests for clarifications or corrections will be sent to the investigator.

The investigator agrees to monitoring of the study by a Sponsor representative and that Regulatory Authorities will have the right from time to time both during and after the course of this trial to inspect the study and review pertinent medical records relating to this clinical trial.

Before, during and after the study, the monitor will have regular contacts with the clinic including visits to confirm that facilities remain acceptable, that the investigational team is adhering to the protocol, that data are being accurately recorded in the CRF and to provide information and support to the Investigator. Monitoring of the study will be carried out by Department of Clinic Trials, Institute of Clinical Science, The Queen Silvia Children's Hospital Gothenburg according to their Standard Operating Procedures (SOP)

A statement will be obtained from each subject's parents/guardians participating in the trial permitting the release of the subject's medical records as necessary for monitoring or inspection by authorized personnel for the Sponsor and Regulatory Authorities.

The investigator is responsible for maintaining a comprehensive and centralized filing system of all study-related (essential) documentation, suitable for inspection at any time by representatives of the Sponsor and Regulatory Authorities.

### **10.8 Protocol Amendments**

All revisions to the protocol should be reviewed and approved by the Sponsor and Insméd prior to submission of the amendment to the regulatory authorities. If the revision is an Administrative Change, the investigator should submit it to the REG for their information. If the revision is an Amendment to the protocol, the Investigator must sign it to verify he/she has read and understands the change. The investigator must submit the Amendment to the REG for review and approval prior to implementation.

If an amendment substantially alters the study design or increases the potential risk to the subject:

- the informed consent form or subject information sheet must be revised and submitted to the REG for review and approval; and
- the approved revised form must signed by both parents/guardians currently enrolled in the study; or
- the new form must be used to obtain consent from new parents/guardians prior to their enrollment into the study.

## **10.9 Retention of Study Records**

ICH-GCP guidelines require the medical records and notes, etc., should be clearly marked and permit easy identification of participation by an individual in the trial.

The files should be archived by the investigator at least 10 years after the study is finished.

The investigator is to record all data with respect to protocol procedures, drug administration, laboratory data, safety data, and efficacy data on the CRFs. Essential documents should be retained until at least 2 years after the last approval of a marketing application in an ICH region and until there are no pending or contemplated marketing applications in an ICH region or at least 2 years have elapsed since the formal discontinuation of clinical development of the investigational product. The investigator should store the study records in a secure location.

## **11 DATA MANAGEMENT AND STATISTICAL METHODS**

The investigator will record all data with respect to the study in the subject's CRFs. This includes, but is not limited to, study procedures, laboratory data and safety-related data.

All corrections on a CRF and on source documents must be made in a way that does not obscure the original entry. The correct data must be inserted, dated and initialed by study center personnel. If the change is not obvious, an explanation should be provided.

Completed CRFs for this study will be forwarded to the sponsor for editing, construction of a quality-assured database, and analysis of the data.

### **11.1 Determination of Sample Size and Statistical Methods**

#### **Primary endpoint**

The primary endpoint is ROP classified as 0,1,2,3,3+ which is the expected possible range of ROP stages that will be encountered in the study based on analysis of infants screen for ROP in Gothenburg through the years 2004 to 2008. This is an ordinal scale with higher numbers indicating a more severe outcome. The proportion of children with each outcome based on register data is given in table below. In this table an anticipated treatment effect is also indicated by presenting expected outcome in the treated group.

| ROP  | 0 | 1 | 2 | 3 | 3+ | Total |
|-------------|----------|----------|----------|----------|-----------|--------------|
| Control (%) | 26       | 15       | 24       | 18       | 17        | 100          |
| Active (%)  | 49       | 19       | 19       | 9        | 4         | 100          |

Percentage distribution of children with different ROP-outcomes. Control group based on register data and active group based on expected treatment effect.

The estimated treatment effect is based on the following assumptions.

- 25 % of the children will not have any benefit from the treatment.
- 25% will have their ROP reduced one step (e.g. from 2 to 1)
- 50% will have their ROP reduced two steps. (e.g. from 3+ to 2)

The null hypothesis to test is if the distribution ( $F$ ) of ROP ( $X$ ) is the same in both treatment groups.

$$H_0 : F_C(X) = F_A(X)$$

$$H_1 : F_C(X) \neq F_A(X)$$

This hypothesis will be tested with the Mann-Whitney test.

In order to have 80% power at a significance level of 5% a sample of 40 subjects per group is needed (80 subjects in total).

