## **5 STUDY SUBJECTS**

### **5.1 Number of Subjects**

For efficacy evaluations, 80 subjects need to be included for statistical considerations. However, to compensate for protocol violations and withdrawals up to 90 subjects will be included (see **11.1 De-termination of Sample Size and Statistical Methods** on page 26).

After the first 20 subjects have been treated and evaluated there will be a safety check to confirm that the safety profile is acceptable and that the assumption of a 50% reduction in ROP incidence is reasonable. A second safety check will be performed after the next 20 subjects.

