## 11.2 Study Populations

All available subjects will be used in the data summaries and the listings of subject data. If a subject is regarded as non-evaluable this subject may be listed separately and not included in the summary statistics.

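### Infants who die before retinopathy of prematurity (ROP) can be staged have no place in the primary scale or the planning figures, so a difference in mortality between arms could bias the ROP comparison in either direction

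*Protocol*

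**What the plan says.** Section 11.1 fixes the endpoint and the test: "The primary endpoint is ROP classified as 0,1,2,3,3+ which is the expected possible range of ROP stages that will be encountered", and "This hypothesis will be tested with the Mann-Whitney test". The control percentages are "based on analysis of infants screen for ROP in Gothenburg through the years 2004 to 2008", so they describe infants who reached screening. The planning rows are "Control (%) | 26 | 15 | 24 | 18 | 17 | 100" and "Active (%) | 49 | 19 | 19 | 9 | 4 | 100". Each sums to 100 over the five stages, with no share for death.

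Infants are eligible if born before 28 weeks (section 5.2). Consent is due within 24 hours of birth (section 7.3), and randomisation takes place at study entry (section 4). The first retinal examination is at four to five weeks of age in section 6.3 and at five to six weeks in section 8.1.

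On losses, section 5.1 says that "to compensate for protocol violations and withdrawals up to 90 subjects will be included". Section 11.2 says: "If a subject is regarded as non-evaluable this subject may be listed separately and not included in the summary statistics". Death is mentioned only in safety recording and reporting (sections 9.1 and 9.2).

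**The concern.** Infants are randomised at birth, while the outcome can first be observed about a month later. The five-stage scale has no level for an infant who dies in between, so that infant cannot contribute to the primary test. An infant who dies after a first examination has a stage on record, but perhaps not the worst stage that would have been reached.

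Death happens after randomisation and could be affected by treatment. If one arm has more deaths, and they fall among infants who would have had severe ROP, the staged infants left in that arm look healthier than those in the other. That arm can then appear to prevent ROP. The reverse also holds: an arm that saves high-risk infants can appear to cause ROP. What is at stake is how far a difference in stage can be read as an effect on the retina. The number of infants left to analyse matters less.

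**Working it through.** **Inputs.** From section 11.1: control 26/15/24/18/17%, active 49/19/19/9/4% (stages 0, 1, 2, 3, 3+), two-sided 5% Mann-Whitney test, 40 per group. From section 5.1 and the synopsis: 90 infants, 45 per arm. Mortality, and the link between death and ROP risk, are assumptions because the protocol gives neither.

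**The plan's own figure.** The stated shifts (25% no change, 25% one step, 50% two steps) applied to the control row give, for stage 0, 26 + 0.75 × 15 + 0.50 × 24 = 49.25%. The full result is 49.25/18.75/19/8.75/4.25%, which matches the table. Simulating the tie-corrected test at 40 per group gives about 79% power, and 80% is reached at 41 to 42 per group. The stated sample size therefore reproduces, provided that every infant counted is staged.

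**Bias with no effect on ROP.** The control row comes from screened infants, so it is used as the distribution among control survivors. Let control mortality be 15% and active mortality 15% plus an excess e. The share of active survivors at stage 3 or 3+ is

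(0.35 × 0.85 − e × s) / (0.85 − e),

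where s is the share of extra deaths falling at those stages. Two links are used:

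- Mild: risk of death weighted 1:1:1:2:3 by stage, so s = (2 × 18 + 3 × 17) / (26 + 15 + 24 + 2 × 18 + 3 × 17) = 87/152 = 57%.
- Extreme: every extra death is at stage 3 or 3+, so s = 100%.

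The test is simulated on 38 control survivors against 36 active (20% mortality) or 34 active (25%):

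| Mortality, control v active | Link | Stage 3 or 3+ among survivors | Trials favouring active (nominal 2.5%) |
|---|---|---|---|
| 15% v 20% | mild | 35% v 34% | about 3.3% |
| 15% v 25% | mild | 35% v 32% | about 4.3% |
| 15% v 20% | extreme | 35% v 31% | about 5% |
| 15% v 25% | extreme | 35% v 26% | about 9.5% |

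At 15% v 15%, total rejection stays at the nominal 5%. In the last row, analysing all 45 v 45 infants with death ranked worse than 3+ favours active in about 1.0% of trials.

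**Opposite direction.** With 20% v 10% mortality and all saved infants at stage 3 or 3+, severe ROP among survivors is 35% in the control arm v (0.35 × 0.80 + 0.10)/0.90 = 42% in the active arm. The test then wrongly favours control in about 8% of trials.

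**Loss allowance.** The allowance is 10/90 = 11.1%. If every death is unstaged and nothing else is lost:

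| Mortality (assumed) | Staged, of 90 | Power under the planned effect | Randomised to keep 80 staged |
|---|---|---|---|
| 10% | 81 | about 79% | 80/0.90 = 89 |
| 15% | 76.5 | about 77% | 80/0.85, about 95 |
| 20% | 72 | 74 to 75% | 80/0.80 = 100 |
| 25% | 67.5 | 71 to 72% | 80/0.75, about 107 |

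**Cost of ranking death worst in the primary test.** With 10% mortality in both arms and 45 per arm, power under the planned effect falls to about 64%.

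**The case against.** Several points on the other side are sound.

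- How deaths are handled, supporting analyses and tables of deaths are often left to a statistical analysis plan, and none is shown here. That is true. But this protocol itself fixes the scale, the planning distributions, the test and the loss allowance, and none of them makes room for death.
- A reader might infer that the protocol orders a survivors-only test, or lets every death be dropped as non-evaluable. It does not say so. Section 11.2 begins from all available subjects, its exclusion wording is permissive and concerns summary statistics, and death is never called non-evaluable. Examinations are weekly, so an infant who dies after the first one may be counted with the stage seen so far. Only deaths before the first examination are necessarily unstaged.
- A reader might infer that the allowance shuts deaths out. Section 10.1 defines discontinuation broadly enough that withdrawals could include them. Even so, the 11.1% is shared with protocol violations, and a larger sample would not remove bias from unequal mortality.
- The 9.5% figure is a corner case. It needs a 10-point excess in mortality with every extra death at stage 3 or 3+. Milder assumptions give 3.3% to 5%.
- Deaths would not be hidden. They are recorded as adverse event outcomes and reported as serious adverse events, and safety checks follow the first 20 and the next 20 infants. But the protocol does not tie deaths by arm to the reading of the primary result.

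**Conclusion.** The point holds as a cheap improvement. Infants who die before their first examination cannot enter the primary test, and neither the planning figures nor the loss allowance names them. Bias arises only if mortality differs by arm and deaths are linked to ROP risk, and it can run either way. Under the assumptions shown, the chance of a false finding in favour of active rises from 2.5% to between about 3.3% and 9.5%, with no inflation at equal mortality. The effect on power is modest: at assumed mortality of 10% to 15%, 90 infants give 79% to 77%, against about 79% at the planned 80.

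Two stronger conclusions might be drawn and are not supported. The documents do not show that the treatment changes mortality, so they do not show that the trial's result will be biased. Nor is the sample size calculation wrong in its arithmetic; it is conditional on every counted infant being staged.

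**What to change.** Keep the stage comparison as the primary analysis, since ranking death worst in the primary test would cost too much power. In section 11.1, add:

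- a prespecified supporting analysis of all randomised infants, with death before the ROP outcome ranked worse than 3+, and one line saying which deaths count as before the outcome;
- deaths by arm shown beside the primary result;
- a statement that any claim of ROP protection will be interpreted in the light of both. This should not be an automatic veto, because a few deaths among 90 infants can be unbalanced by chance.

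In section 5.1, state that the increase from 80 to 90 must also cover deaths, give the assumed mortality, and restate power for the number expected to be staged.

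The cost is one extra analysis, on data already collected as safety events, and a slightly lower stated power.

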### 4 STUDY DESIGN

The study is a Randomised Intervention, Single-Center Study to Determine the Role of Fatty Acids in Serum and Breast Milk in preventing Retinopathy of Prematurity

Subjects who meet all inclusion and none of the exclusion criteria will be enrolled into the study. Upon entry into the study, subjects will be randomized and given a unique subject number.

A randomised intervention study of 45+45 (number based on power analysis regarding up to date ROP frequency, see 5.1 and 11.1) infants without major malformations born with a gestational age less than 28 weeks + 0 days will be performed.

Randomization of the patients to either

- 1) Conventional fatty acid supplementation regime with Clinoleic (with Vitalipid infant and Soluvit supplementation) to the preterm infant

Or

- 2) SMOFlipid® (with Vitalipid infant and Soluvit supplementation), where the quotient of Omega 6:3 is 2.5:1 in order to mimic the physiologic relation of FAs in cord blood from birth, to the preterm infant.

Thus there is one group of infants (n=45) that will receive Omega-3 in the fatty acid supplementation. The time on parenteral nutrition and the amount of fatty acids given will be according to clinical routines. The randomization of the patients will be performed by the controller of the study Randomization will be in blocks with 10 children in each block.

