## Secondary endpoints

Important secondary endpoints are:

- Body weight
- Length
- Head circumference

These will be modelled by a linear mixed effects model. Subject will be used as a random factor, and *GA* and *treatment* will be used as fixed factors. The hypothesis of interest is if there is a significant difference in the slope, i.e. that the growth rate is different in the two groups.

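### The primary ROP test leaves out gestational age at birth, which is held for every infant and which randomisation does not balance: a valid test, but one that may waste power and does not correct chance imbalance

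*Protocol*

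**What the plan says.** Section 11.1 of the protocol defines an ordinal outcome ("The primary endpoint is ROP classified as 0,1,2,3,3"+) and a null hypothesis of equal distributions in the two arms. It then names the test: "This hypothesis will be tested with the Mann-Whitney test". No covariate or stratum is attached.

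The sample size rests on that test. The target is 80% power with 5% significance, and the section concludes that "a sample of 40 subjects per group is needed (80 subjects in total"). Section 5.1 raises enrolment to as many as 90 to allow for violations and withdrawals.

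On allocation, section 4 says only "Randomization will be in blocks with 10 children in each block". Blocking keeps the numbers per arm equal; it does nothing for the mix of gestational ages. Section 5.2 makes gestation below 28 weeks an inclusion criterion, so gestational age at birth is recorded for every infant before randomisation.

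**The concern.** Section 1 describes retinal vascularisation as running from the fourth gestational month to term, with ROP following when it is interrupted. Gestational age at birth is therefore a natural candidate predictor of ROP stage. Section 6.2 adds that the most immature infants may stay longer on parenteral feeding, so maturity may also be tied to length of exposure to the study lipid.

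If gestational age does predict stage in this population, an unadjusted rank test treats that predictable spread as noise. A chance difference in maturity between two arms of 40 then passes straight into the comparison, because neither the allocation nor the analysis deals with it. Power is close to the 80% target with nothing to spare at 40 evaluable infants per arm, so an efficiency gain at no cost in infants is worth having.

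**Working it through.** **Inputs from section 11.1.** "Control (%) | 26 | 15 | 24 | 18 | 17 | 100" and "Active (%) | 49 | 19 | 19 | 9 | 4 | 100", for stages 0, 1, 2, 3, 3+ and total; 40 per group; 5% level, taken as two-sided because the alternative is inequality.

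**Step 1: the plan's own figures.** The stated assumptions (25% no benefit, 25% one step, 50% two steps) applied to the control row give:

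- stage 0: 0.26 + 0.75 × 0.15 + 0.50 × 0.24 = 0.4925
- stage 1: 0.25 × 0.15 + 0.25 × 0.24 + 0.50 × 0.18 = 0.1875
- stage 2: 0.25 × 0.24 + 0.25 × 0.18 + 0.50 × 0.17 = 0.1900
- stage 3: 0.25 × 0.18 + 0.25 × 0.17 = 0.0875
- stage 3+: 0.25 × 0.17 = 0.0425

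This agrees with the active row. The probability that a control infant has the worse stage, ties counted half, is 0.49 × 0.87 + 0.19 × 0.665 + 0.19 × 0.47 + 0.09 × 0.26 + 0.04 × 0.085 = 0.669. Simulating the tie-corrected two-sided Mann-Whitney test 200,000 times gives 78.9% power at 40 per group and 83.5% at 45. Noether's formula with tie correction gives a total of 85.3, about 43 per group. The stated 40 reproduces to within about a point of power.

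**Step 2: power with adjustment, by odds ratio per week.** The protocol gives no ROP rates by gestational week, so the strength is assumed. Gestational age is drawn from an assumed mix of 10/17/21/25/27% for 23 to 27 weeks. The control margin is held at the table values, and active infants move 0, 1 or 2 stages with probability 0.25/0.25/0.50. Rank ANCOVA regresses the ROP ranks on the gestational-age ranks and compares the residuals between arms. With 6,000 trials of 40 per arm, the simulation error is √(0.8 × 0.2 / 6,000), or 0.5 points.

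| Assumed odds ratio for higher stage, per week | Mann-Whitney | Rank ANCOVA |
|---|---|---|
| 1 or 0.85 | 79-80% | 79% |
| 0.7 | 79-80% | 81% |
| 0.5 | 79-80% | 86% |
| 0.4 | 79-80% | 90% |

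Null rejection was about 4.5-5.6%.

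**Step 3: a second model as a check.** Here ROP is a cut latent normal variable with both arms fixed at the table values, and its correlation with gestational age is assumed (20,000 trials per setting).

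| Assumed correlation | Mann-Whitney | Rank ANCOVA |
|---|---|---|
| 0 | 79% | 78% |
| 0.2 | 79% | 80% |
| 0.3 | 79% | 81% |
| 0.4 | 80% | 84% |
| 0.5 | 79% | 87% |
| 0.6 | 79% | 91% |

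At correlation 0.4, the adjusted test with 40 per arm (84%) does about as well as the unadjusted test with 45 (83.5%).

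**Step 4: chance imbalance.** In standard deviations of gestational age, the difference in arm means has standard error √(2/40) = 0.224. A difference above 0.3 SD therefore occurs with probability 2 × P(Z > 0.3/0.224) ≈ 18%. In those trials, with no treatment effect, the unadjusted test rejects about 6%, 7%, 9%, 10% and 14% of the time at correlations 0.2, 0.3, 0.4, 0.5 and 0.6. The adjusted test stays at about 4-5%. Overall the unadjusted rate remains about 5%, because better-balanced trials reject less often. At correlation 0.5, for example, (0.049 − 0.176 × 0.102) / 0.824 = 3.8%.

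**Step 5: does a proportional-odds model suit?** Cumulative odds ratios from the two rows are:

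- stage 0: (0.49/0.51) / (0.26/0.74) = 2.7
- stage 1 or less: (0.68/0.32) / (0.41/0.59) = 3.1
- stage 2 or less: (0.87/0.13) / (0.65/0.35) = 3.6
- stage 3 or less: (0.96/0.04) / (0.83/0.17) = 4.9

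They rise steadily, so the planned effect is not a proportional-odds effect.

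**The case against.** The Mann-Whitney test is valid for an ordinal outcome and matches the stated null hypothesis. Randomisation protects the overall error rate, chance imbalance included, and the sample size reproduces. All of this stands: the point is one of efficiency and of error conditional on imbalance.

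The protocol nowhere says how strongly gestational age predicts ROP among infants below 28 weeks, and so narrow a range may weaken the relation. This also stands. At an odds ratio per week of 0.85 or a correlation of 0.2 the gain is nil to about 1 point, so a large gain cannot be read from the documents.

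A statistical analysis plan that is not shown might add adjusted analyses. It could do so as support, but it could not make one of them primary without departing from section 11.1, which names the test and sizes the trial on it.

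Three stronger readings are tempting and are not supported.

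- A reader might infer that the plan contradicts itself by adjusting growth for gestational age but not ROP, since GA and treatment "will be used as fixed factors" in the growth model. That model tests a difference in slope and names no other time variable. The protocol also uses gestational weeks for ages after birth, as in the study events table, so GA there may be the time axis.
- A reader might infer that the sample size is wrong or the 5% level inflated. Steps 1 and 4 show otherwise.
- A reader might fault the absence of an effect estimate and confidence interval. That detail is commonly left to the analysis plan.

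**Conclusion.** The concern holds as a matter of efficiency and of unprotected chance imbalance. Section 11.1 fixes an unadjusted primary test, section 4 does not balance gestational age, and gestational age at birth is in hand for every infant. Alpha and the sample size are not in error.

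The size is conditional on an assumed association: no gain at an odds ratio per week of 1 to 0.85, about 1-2 points of power at 0.7, about 6-7 at 0.5 and about 10-11 at 0.4. The odds-ratio figures also rest on an assumed gestational-age mix; the correlation model, which does not use that mix, shows the same pattern. Because the possible loss is about 1 point and the possible gain several times that, the change is worth making, but the plan is not invalid without it.

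**What to change.** In section 11.1, name as primary a rank test adjusted for gestational age at birth: either rank ANCOVA using gestational age in weeks, or a van Elteren test over a few gestational-age bands fixed in advance. Keep the unadjusted Mann-Whitney test as a supportive analysis and leave 40 evaluable infants per group unchanged. A proportional-odds common odds ratio may be reported as a summary, but should not carry the primary test, because the planned effect does not follow that model (step 5).

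The cost is a wording change, with no new data and no extra infants. If gestational age turns out not to be prognostic, the loss is at most about 1 point of power for rank ANCOVA or 2 points for van Elteren. The change should be settled by people who have not seen ROP results by arm, including any from the checks that section 5.1 places after the first 20 and the next 20 subjects.
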